### Participants

Participants will be members of staff working in one of four NHS Trusts in the South of England (three mental health Trusts and one community Trust) with each Trust employing between 2500 and 5000 members of staff. Inclusion criteria are that participants (1) are employed by (or working in an honorary/voluntary capacity for) one of the four NHS trusts, (2) are currently in work (i.e. not currently on sickness absence), (3) have sufficient English language ability to understand intervention information and questionnaire content and (4) are adults (aged 18 years or older). There are no exclusion criteria.

### Procedure

Recruitment is planned to take place between July and December 2017. The Consolidated Standards of Reporting Trials (CONSORT) diagram showing participant flow through the study is shown in Fig. 1. The study will be advertised to all Trust staff through adverts placed on intranets and staff bulletins. In addition, information about the study will be emailed to all staff. Participants consenting to take part in the study will first choose their preferred intervention. Staff can take part in one of the two studies, but not both. This will be checked to ensure that all consenting participants are enrolled in one of the two studies only. Following consent, participants will be sent a standardised e-mail by the research team containing a link to the baseline assessment measures hosted on Qualtrics based on their selected intervention (Time 0). Upon completion of baseline measures, participants will be randomised to their preferred intervention or to the wait-list for their preferred intervention. They will be sent a standardised e-mail informing them of their allocation and details of their intervention. After participants have completed their intervention or wait-list time period, they will be sent a standardised e-mail asking them to complete post-intervention measures online (Time 1). MBCT-L participants will be sent the link to post-intervention measures immediately after completion of the intervention. CBT participants will be invited to complete post-intervention measures one month after workshop completion. The research team will not be present for any of the online assessments (at baseline and post-intervention); measures will be completed by participants online and in their own time. To promote study retention, where necessary participants will be emailed at weekly intervals for up to 4 weeks with a reminder to complete their post-intervention assessment. Potential errors with data entry will be minimised as data will be entered by participants online.

**Fig. 1 Fig1:**
[figure not shown]
CONSORT flow diagram showing participant flow through the study. NHS, National Health Service; CBT, cognitive behavioural therapy; MBCT-L, mindfulness-based cognitive therapy for life

Ten participants from each intervention arm, who complete both baseline and post-intervention measures, will be invited to take part in an optional phone interview about their experiences of their preferred intervention.

### Interventions

#### Mindfulness-based cognitive therapy for life

MBCT-L [5] is an adaptation of MBCT originally developed by Segal, Williams and Teasdale [35, 36]. MBCT was originally developed for people with a history of recurrent depression at risk of depressive relapse and integrates CBT strategies with mindfulness practice and inquiry about practice. MBCT-L was developed to be applicable to the general population across the spectrum of wellbeing and draws on the same structure and techniques as MBCT. MBCT-L is an 8-week group intervention (with a pre-course orientation session) where participants are guided in mindfulness practice and engage with a range of CBT strategies. In this study, each group will be led by one or two MBCT teachers and will consist of up to 15 participants. Each session will take 2 h and participants will be invited to complete approximately 40 min per day of mindfulness practice and other home tasks. Content in the sessions will include guided mindfulness practices, inquiry into experiences following practices, weekly homework review, and teaching/discussion of CBT skills. The teachers leading the groups will have completed MBCT teacher training and will meet MBCT teacher criteria set out by the UK Network of Mindfulness-Based Teacher Training Organisations. Teachers will have completed additional MBCT-L training. Supervision will be provided on at least three occasions per group by a teacher who meets the supervisor criteria set out by the UK Network of Mindfulness-Based Teacher Training Organisations and who has attended 2-day MBCT-L training. Intervention completion is defined as attending at least four of the eight sessions.

#### Cognitive behavioural therapy

This 1-day (6 h) workshop will teach participants CBT approaches to managing work-related stress. The workshop is divided into three broad sections. The first part of the workshop introduces a CBT formulation of work-related stress, drawing on the transactional theory of stress [25, 26] and the CBT maintenance cycle highlighting the inter-relationships between thoughts, feelings, physical sensations and behaviours, within work (and other) contexts. Participants will have the opportunity to formulate their own work-related stress experiences within these frameworks. The second part of the workshop overviews strategies to intervene in the maintenance cycle, with a particular focus on cognitive and behavioural strategies. The third part of the workshop encourages participants to identify specific, measurable, attainable, relevant and timely (SMART) goals, drawing on learning from the workshop and making a commitment between participants to progress towards these goals. Each workshop will consist of up to 20 participants and will be facilitated by two mental health practitioners, who demonstrate the following skills and experience between them: (1) a qualified CBT therapist or practitioner psychologist who works with CBT as their primary therapeutic model; (2) experience of facilitating therapeutic workshops or groups and (3) a senior grade within their NHS trust or a registered mental health professional with significant experience working in their NHS trust. All facilitators will attend a 1-day training event led by a clinical psychologist and CBT therapist who developed the workshop materials and will receive at least one telephone consultation session. Intervention completion is defined as attending the whole of the 1-day workshop.

## Measures

### Primary outcome

#### Stress

The primary outcome measure will be the 7-item stress subscale from the 21-item short version of the Depression, Anxiety, and Stress Scales (DASS-21) [27]. The stress subscale of the DASS-21 measures the severity of core symptoms associated with stress. Participants are asked to indicate the presence of each symptom over the past week. Responses are given on a 4-point Likert scale, ranging from 0 (never) to 3 (almost always). The DASS-21 stress subscale has been found to have good internal consistency and convergent and discriminant validity [2, 19].

### Secondary outcomes

#### Sickness absence

Sickness absence data will be obtained from Human Resources departments in the NHS trusts. This will be recorded as the number of sickness absence days taken in the month following the end of the intervention period. Equivalent data from the same 1-month period in the previous calendar year will be obtained as a baseline measure for each participant. Reasons for sickness absence will not be recorded. This is to respect participant confidentiality.

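### In the MBCT-L trial the sickness-absence month falls after the stated wait-list period, so the text does not secure an untreated control for secondary hypothesis (1)

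*Protocol article*

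**What the plan says.** All references are to the protocol article.

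- **Sickness absence.** The outcome is a count of days from HR records: "This will be recorded as the number of sickness absence days taken in the month following the end of the intervention period". The baseline is the matching month a year before: "Equivalent data from the same 1-month period in the previous calendar year will be obtained as a baseline measure for each participant". No other follow-up window is given, and the sentence serves both trials.
- **Procedure, comparator.** After baseline measures, "participants will be randomised to their preferred intervention or to the wait-list for their preferred intervention".
- **Procedure, general timing of Time 1.** "After participants have completed their intervention or wait-list time period, they will be sent a standardised e-mail asking them to complete post-intervention measures online (Time" (the quote stops just before the numeral).
- **Procedure, timing by trial.** For MBCT-L: "MBCT-L participants will be sent the link to post-intervention measures immediately after completion of the intervention". For CBT: "CBT participants will be invited to complete post-intervention measures one month after workshop completion".
- **Procedure, reminders.** Non-responders are e-mailed weekly for up to four weeks.
- **Background, hypotheses.** Lower sickness absence than wait-list is secondary hypothesis (1) in both trials.
- **Measures, end of the engagement section.** HR data are requested only when the study ends.

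**The concern.** A wait-list control is informative for as long as the controls are still waiting. The protocol states when waiting ends and when absence is counted. In MBCT-L the second period begins where the first stops. Nothing in the text shown keeps MBCT-L wait-list staff off their own course while their absence days are being counted.

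If they start during that month, the comparison is between staff who have finished the course and staff who are part-way through it. Any benefit gained early in the course reduces the difference between arms, and a null result could be misread as no effect on absence. This matters because the Background names the lack of randomised evidence on absence as the first gap, and the Discussion says an effect would give employers an economic reason to widen access.

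A smaller point follows from the same timing. The reminder period runs for up to four weeks after Time 1, and the DASS-21 stress items ask about the past week. A late-responding MBCT-L control could therefore report stress after starting a course, if courses open that early.

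**Working it through.** **1. The sequence in each trial**

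| | MBCT-L | CBT |
|---|---|---|
| Intervention ends | last weekly session | workshop day |
| Time 1 (follows completion of the wait-list period) | immediately after the course | one month after the workshop |
| Absence month | from Time 1 to one month after it | from the workshop to Time 1 |
| Position relative to the stated control period | after it | inside it |

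This uses only the Procedure and Sickness absence sections, and dates the control arm's Time 1 in line with its intervention arm.

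**2. The plan's own figures**

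There is no effect size, standard deviation or power figure for absence. The sample-size figures concern stress only: 140 completers and 40% non-completion give 140 / (1 − 0.40) = 233.3, rounded up to 234, or 117 per arm. Because HR records do not depend on questionnaire completion, 117 per arm is the largest number available for absence.

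**3. Possible dilution (assumed inputs)**

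Assumptions: the month is four weeks; wait-list benefit t weeks after their own start is min(t/T, 1) of the full effect; T is 8 weeks (course length) or 4 weeks (half of it). The dilution s is the average of this over the four-week window.

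- Start at Time 1, T = 8: (1/4) × ∫₀⁴ t/8 dt = (1/4) × 1 = 0.25
- Start at Time 1, T = 4: (1/4) × ∫₀⁴ t/4 dt = (1/4) × 2 = 0.50
- Start two weeks later, T = 8: (1/4) × ∫₀² t/8 dt = (1/4) × 0.25 = 0.063
- Start two weeks later, T = 4: (1/4) × ∫₀² t/4 dt = (1/4) × 0.5 = 0.125
- Start after the month: 0

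With weekly sessions from Time 1, four would fit in the window. The protocol sets its own threshold there: "Intervention completion is defined as attending at least four of the eight sessions".

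**4. What dilution would do to power (assumed effect sizes)**

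Power ≈ Φ(d(1 − s)√(n/2) − 1.96), with n = 117 per arm and two-sided 5%:

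| Assumed true d | s = 0 | s = 0.25 | s = 0.50 |
|---|---|---|---|
| 0.20 | 0.33 | 0.21 | 0.12 |
| 0.30 | 0.63 | 0.41 | 0.21 |
| 0.50 | 0.97 | 0.82 | 0.48 |

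The sample size needed for the same power grows by 1/(1 − s)²: 1.78 times at s = 0.25 and 4 times at s = 0.50. Absence days are skewed counts, so these figures only illustrate scale.

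**The case against.** The strongest reply is that the harm depends on a date the text does not give. The Procedure places the Time 1 e-mail after the waiting period; it does not say that courses open to controls that day. Fig. 1 (participant flow) and Fig. 2 (schedule of enrolment, interventions and assessments) are not reproduced, and either may show the date, as may the full protocol. **This stands.** A reader might infer that controls do start in that month and that the absence result will be diluted. The documents do not support that inference.

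A reader might also infer that absence is measured outside the randomised comparison. It is not. HR data relate to staff as randomised, and the Planned data analysis section includes an intention-to-treat analysis. Only the question answered may change.

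The dilution figures rest entirely on assumed start dates and an assumed build-up. Four sessions is an attendance threshold and not evidence of benefit, and a control would reach it only near the end of the month. The orientation session before the course could push session 1 later still. **All of this stands**, so the figures are a range that includes zero.

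A window after the course is also a sensible choice, because the hypothesis is post-intervention and a window during the course would catch a partly treated intervention arm. The phrase 'intervention period' can fairly be read as a common period applied to both arms. Neither point removes the problem: a post-course window is sound only if controls wait through it, and the stated rules end the wait before it begins. The point therefore rests on how two stated timings interact, as well as on an omitted date.

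**Conclusion.** The concern holds in limited form. As written, the MBCT-L absence month lies wholly after the stated control period, whereas the CBT absence month lies inside it. Whether this costs anything depends on when MBCT-L wait-list courses begin.

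If they begin after the month, nothing is lost. If they begin within it, the intention-to-treat comparison stays valid but estimates early versus delayed MBCT-L, biased towards no difference. The loss is 6% to 13% of the contrast for a start two weeks after Time 1 and 25% to 50% for a start at Time 1, on the assumption of linear build-up over eight or four weeks. With an assumed true d of 0.30 and 117 per arm, a 25% to 50% loss would take power from 0.63 to between 0.41 and 0.21.

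The point concerns a secondary outcome. The late-reminder exposure of the stress outcome is equally conditional, and the documents do not show that the primary comparison is affected. It is still worth correcting, because absence is secondary hypothesis (1) and the correction is cheap.

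**What to change.** **For the MBCT-L trial:**

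1. Define the wait-list period as running to the end of the sickness-absence month. This also covers the four-week reminder period. If Figs 1 and 2 or the full protocol already provide for this, say so in the Sickness absence and Procedure sections.
2. Date Time 1 and the absence month in both arms from the same course dates, so that each control's window matches that of the intervention participants randomised alongside them.
3. If some wait-list groups have already started within the month, also request HR absence days for the part of the period in which controls were still waiting. Use the same window in both arms and the same calendar dates one year earlier as baseline; shortening only the follow-up window would break its match with the one-month baseline. Report the full-month result as early versus delayed course.

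**Cost:** changes to wording and to the dates in the HR request, which is not made until the study ends. MBCT-L wait-list staff may wait up to about one month longer. For groups already started, the additional window is shorter and captures fewer absence days.

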This protocol is for two RCTs examining the effectiveness of two interventions for staff working in the NHS: (1) MBCT-L and (2) CBT-based stress management. Staff will select one of these two interventions and then will be randomly assigned to either the intervention arm or to the wait-list arm within their preferred choice. Our intention in offering staff a choice between these two interventions is to increase accessibility and choice, acknowledging that no one intervention is likely to meet the needs of all staff.

Given the existing evidence for these interventions is predominantly in stress-reduction, the primary hypothesis is that both interventions will be more effective than the wait-list at reducing stress post-intervention. Secondary hypotheses are that both interventions will be more effective than the wait-list post-intervention in: (1) reducing sickness absence; (2) improving compassion for others; (3) reducing anxiety symptoms; (4) reducing depression symptoms; (5) reducing work-related burnout; (6) improving compassion for self; (7) improving wellbeing; (8) reducing presenteeism and (9) improving mindfulness (in MBCT-L participants only). We also plan to explore participants’ experiences of their chosen intervention using thematic analysis of semi-structured interviews.

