#### Presenteeism

This will be measured using the 3 questions that assess presenteeism, from the Institute for Medical Technology Assessment Productivity Cost Questionnaire (iMTA PCQ) [6]. The overall iMTA PCQ is designed to assess and value productivity losses. The 3 presenteeism questions ask participants (1) if over the past 4 weeks, they worked whilst experiencing physical or psychological problems (yes/no) and if so, (2) how many days at work they were bothered by these problems and (3) how their performance on these days compared to their performance on normal working days. The third question is measured on a 10-point rating scale, ranging from 0 (on these days I could not do anything) to 10 (I was able to do just as much as I normally do). The first 2 questions originate from the short form of the Health and Labour Questionnaire (SF-HLQ) [40] and the third question from the Productivity and Disease Questionnaire (PRODISQ) [22]. The 3 questions have been found to have good test-retest reliability [6].

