### Planned data analysis

The intention in providing two interventions is to increase choice and accessibility. The intention is not to compare the effectiveness of the CBT intervention directly with the MBCT-L intervention and any such comparison would be problematic given the potential for selection bias (i.e. participants preferring MBCT-L may differ in a number of ways from participants preferring the CBT workshop). Intervention preference will be reported as the number and percentage of participants choosing each intervention type; however we would urge caution when interpreting these data as participant preferences may be driven by practicalities (e.g. location and dates of available courses) as much as by intervention preference.

Between-group differences at baseline on key demographic variables (age, gender, ethnicity, NHS trust, pay band and years working in the trust) and all outcome measures will be reported for each study. Findings will be reported for both intention-to-treat and per-protocol analyses. Hypotheses will be tested using mixed analysis of variance (ANOVA) for each intervention separately, with time (baseline, post-intervention) as the within-group variable and intervention arm (intervention, wait-list) as the between-group variable. Post-intervention between-group effect sizes (Cohen’s *d*) and 95% confidence intervals will be reported. Interaction effects will be followed up with within-group *t* tests, with Cohen’s *d* effect sizes and accompanying 95% confidence intervals for within-group change.

Qualitative data will be transcribed and thematic analysis will be performed in accordance with the Braun and Clarke [7] protocol. This will involve the researcher leading on the qualitative aspect of the study reading and re-reading transcripts, allocating codes to single units of meaning within each transcript, identifying sub-themes representing lower-order categories of meaning across participants (within CBT/MBCT-L separately) and finally identifying higher-order themes and the relationship between themes and sub-themes (for CBT/MBCT-L separately). This will be conducted under supervision from the lead author. Credibility will be checked through supervision and will be indicated through providing comprehensive extracts from participants to illustrate each theme and sub-theme.

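### Sickness absence is tested as change from one month a year earlier, which loses precision that baseline adjustment would keep, and Cohen's d is a poor scale for days absent

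*Protocol article*

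**What the plan says.** Under Secondary outcomes, Sickness absence, the protocol article takes the outcome from HR departments: "This will be recorded as the number of sickness absence days taken in the month following the end of the intervention period". For baseline, "Equivalent data from the same 1-month period in the previous calendar year will be obtained as a baseline measure for each participant". The Background places this outcome first among nine secondary hypotheses: "1) reducing sickness absence; (2) improving compassion for others".

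Planned data analysis then gives one rule for every hypothesis: "Hypotheses will be tested using mixed analysis of variance (ANOVA) for each intervention separately, with time (baseline, post-intervention) as the within-group variable", with arm as the between-group factor. No outcome is exempted, and no separate model or transformation is given for absence. Two summaries go with the test. One is "Post-intervention between-group effect sizes", meaning Cohen's d with 95% confidence intervals. The other applies when an interaction is found: "Interaction effects will be followed up with within-group" t tests.

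The document gives no absence rate, mean, standard deviation or month-to-month correlation.

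**The concern.** In a two-time-point mixed ANOVA the treatment effect is carried by the time-by-arm interaction, so the planned test compares arms on post-intervention days minus days in a single month a year earlier. One month's absence is a short, erratic window. Eligibility also requires staff to be at work on entry, so many zeros and a weak link between the two months are plausible. Subtracting a weakly related baseline adds its noise to the outcome without removing much.

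The Discussion says effects on absence would particularly interest employers and give an economic reason to widen access. A test that discards precision makes a real effect easier to miss. A standardised difference also does not tell an employer how many days, or how many absent staff, are at issue.

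**Working it through.** The document has no figure of its own for this outcome to reproduce. The only input from its sample-size section is the recruitment target: 140 / (1 − 0.40) = 233.3, rounded up to 234 per trial, or 117 per arm at 1:1.

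**Step 1: what the interaction tests.** With two time points, the interaction F statistic is the square of the t statistic comparing mean change between arms.

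**Step 2: variances.** Let both months have variance σ² and correlation r. Per participant, the variance behind the between-arm contrast is:

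- change (planned test): 2σ²(1 − r)
- post-intervention days only: σ²
- post-intervention days adjusted for baseline (ANCOVA): σ²(1 − r²)

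Change against ANCOVA is therefore 2(1 − r)/(1 − r²) = 2/(1 + r). Change against post-only is 2(1 − r), which exceeds 1 whenever r < 0.5.

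**Step 3: numbers.** The values of r are assumptions. The last column is 234(1 + r)/2, the number of participants on whom an ANCOVA would match the planned test on 234.

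| r | change / ANCOVA | change / post-only | equivalent N |
|---|---|---|---|
| 0 | 2.00 | 2.0 | 117 |
| 0.1 | 1.82 | 1.8 | 129 |
| 0.2 | 1.67 | 1.6 | 140 |
| 0.3 | 1.54 | 1.4 | 152 |
| 0.5 | 1.33 | 1.0 | 176 |
| 0.7 | 1.18 | 0.6 | 199 |

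**Step 4: does this carry over to zero-heavy counts?** Simulations used 117 per arm. With 20% of the wait-list arm having any absence, halving the risk means about 23 people with absence against about 12 (117 × 0.20 = 23.4; 117 × 0.10 = 11.7). With r about 0.04 to 0.10, power was:

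- planned change test: 17–21%
- ANCOVA: 34–36%
- Poisson regression with robust standard errors and baseline as covariate: 34–37%

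A wider grid (2,000 runs per cell, risk halved) gave:

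| zeros | r of days | change | post-only | ANCOVA | robust Poisson |
|---|---|---|---|---|---|
| 85% | 0 | 15% | 30% | 30% | 31% |
| 75% | 0.18 | 25% | 44% | 46% | 44% |
| 65% | 0.38 | 44% | 61% | 67% | 65% |

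Type I error of the change test was 4–5%. That of robust Poisson ran slightly high in most settings (4–7%), so its power is if anything flattered.

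**Step 5: source of the loss.** Moving from change to ANCOVA recovers the power, and moving on to a count model adds nothing. A rank test did better in the grid (44–86%), but there the effect acted on whether a person was absent at all. The rank test also gives no estimate in days, so I do not rest the point on it.

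**The case against.** The best defence is that the planned test is valid and the planned estimate is not a change score. Both parts stand. Type I error held near 5% despite the skew. The Cohen's d with its confidence interval is a post-intervention comparison, whose variance relative to baseline adjustment is only 1/(1 − r²): 1.00 at r = 0 and 1.10 at r = 0.3. So the loss of 1.54 to 2.0 attaches to the hypothesis test and not to the reported effect size. It is also true that zero-heaviness and weak correlation are assumptions, that absence leads the secondary outcomes only by list order, and that power is low either way: for a 30% reduction it was 10% with the planned test and 17% with robust Poisson.

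Three stronger readings are tempting but unsupported:

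- **That the normal model is what costs power.** The simulations put the loss on the subtraction, since ANCOVA and the count model perform alike.
- **That absence will be analysed only in people with complete data.** The 140 completers are a sample-size target for stress. Planned data analysis promises intention-to-treat as well as per-protocol results, and absence is requested from HR at the end of the study, apart from the questionnaires.
- **That the same rule breaks presenteeism by comparing subsets formed after randomisation.** The items "ask participants (1) if over the past 4 weeks, they worked whilst experiencing physical or psychological problems (yes/no) and if so" go on to two conditional questions, but the article states no scoring rule and does not say that those questions are analysed only in people answering yes. Scoring may properly sit in a document not shown.

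**Conclusion.** The concern holds as a matter of efficiency and reporting. For sickness absence the protocol fixes a change-score test against a single month a year earlier. Given equal variances at the two times, that test has more variance than baseline adjustment at every r below 1, and more than ignoring baseline when r is below 0.5. For an assumed r of 0 to 0.3 the excess is 2.0 to 1.54 times, and in the 20%-absence illustration power falls from 34–37% to 17–21%. The direction does not depend on the assumed absence rate, but the power figures do. False positives are not inflated. Cohen's d on days absent is a separate, smaller fault of scale.

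Severity is minor to moderate. This is one secondary outcome, the primary stress analysis is not at issue here, and a one-month window leaves power low even after the change.

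**What to change.** For sickness absence, replace the interaction test with a comparison of post-intervention days between arms, adjusted for baseline days, in all randomised participants with HR data. Either of these would do:

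- Poisson or negative binomial regression with robust standard errors
- ANCOVA with robust or bootstrap standard errors

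In place of Cohen's d, report a rate ratio or a difference in mean days with a 95% confidence interval, and the proportion in each arm with any absence. State a rule for participants who have no record from a year earlier, such as recent joiners. Honorary and voluntary workers, whom the eligibility criteria admit, may also lack one.

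The cost is a few sentences of analysis wording. The HR extract is the same and no further data are collected. Because absence data are requested only at the end of the study, the change can be made before anyone has seen them.
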